#### *Recruitment & the determination of eligibility*

Participants are recruited from general practitioners (GPs) based in the Primary Care Trusts (PCTs) of central and north London (including some PCTs on the outskirts of these areas). In all, 425 practices have been approached, with 119 agreeing to refer. Each is sent a pack containing information sheets for referrers and participants, eligibility criteria, referral forms, leaflets, and posters for the waiting area. In addition, members of the research team visit practices to discuss the trial, TRD and the test treatment.

Participating practices then refer potential participants whom they consider meet the eligibility criteria (see Table 1).

**Table 1 T1:** TADS Eligibility Criteria

**Patient Eligibility Criteria**	
**Inclusion Criteria**	**Exclusion Criteria**
Major Depressive Disorder or Dysthymia	Recent (previous five years) history of psychosis
Minimum of a two-year history of depression	Recent (previous five year) history of bi-polar disorder
At least two previous failed treatment attempts, one of which was with an anti-depressant	Moderate or severe learning disabilities
Age 18 – 65	Recent history (previous two years) of psychiatric input for, or diagnosis of, substance dependency (alcohol abuse ≥21 units/week; drug abuse ≥ 4/week)
Able to speak conversational English and be seen at the Tavistock Clinic London	Patients currently in psychological therapy
Willing to enter a randomised control trial	Patients who have received psychoanalytic psychotherapy in the previous two years

Two research interviews are then used to verify eligibility criteria and to confirm that these referrals in fact meet DSM-IV criteria for Major Depressive Disorder (assessed using the Structured Clinical Interview [SCID-I]) and show a minimum symptom severity score of 14 on the HRSD or 21 on the BDI-II.

Every subject meeting the criteria is then seen by an experienced clinician, trained in psychoanalytic psychotherapy with adults, using the Tavistock Psychodynamic Interview (TPI). The research aspect of the instrument is described in detail below but it is also employed at this stage to assess the risk of suicide or of other psychiatric emergencies. As well, the interviewer seeks to identify any participant in whom the stress of psychotherapy might trigger a psychotic decompensation. Any such patient would be excluded on ethical grounds, although in the event no subject was excluded on this basis. No selection was made on the basis of any assessment of the subjects’ presumed suitability or unsuitability for psychoanalytic psychotherapy.

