**Methods/Design:**

INDEX GROUP: Patients with treatment resistant/treatment refractory depression. DEFINITION & INCLUSION CRITERIA: Current major depressive disorder, 2 years history of depression, a minimum of two failed treatment attempts, ≥14 on the HRSD or ≥21 on the BDI-II, plus complex personality and/or psycho-social difficulties. EXCLUSION CRITERIA: Moderate or severe learning disability, psychotic illness, bipolar disorder, substance dependency or receipt of test intervention in the previous two years. DESIGN: Pragmatic, randomised controlled trial with qualitative and clinical components. TEST INTERVENTION: 18 months of weekly psychoanalytic psychotherapy, manualised and fidelity-assessed using the Psychotherapy Process Q-Sort. CONTROL CONDITION: Treatment as usual, managed by the referring practitioner. RECRUITMENT: GP referrals from primary care. RCT MAIN OUTCOME: HRSD (with ≤14 as remission). SECONDARY OUTCOMES: depression severity (BDI-II), degree of co-morbid disorders Axis-I and Axis-II (SCID-I and SCID-II-PQ), quality of life and functioning (GAF, CORE, Q-les-Q), object relations (PROQ2a), Cost-effectiveness analysis (CSRI and GP medical records). FOLLOW-UP: 2 years. Plus: a). Qualitative study of participants’ and therapists’ problem formulation, experience of treatment and of participation in trial. (b) Narrative data from semi-structured pre/post psychodynamic interviews to produce prototypes of responders and non-responders. (c) Clinical case-studies of sub-types of TRD and of change.

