### The outcome measures

#### *Primary outcome*

In psychotherapy and antidepressant medication outcome research, the Hamilton Rating Scale of Depression (HRSD, [44]) is the most widely used interview-based measure of depressive severity [62]. Independent, double-rated HRSD scores have been chosen as the trial’s primary index of depression severity. The HRSD is a structured interview which quantifies the severity of depressive symptoms in patients already diagnosed as suffering from depressive disorder. The psychometric properties of the instrument are acceptable [63]. In addition to categorical depressed/not depressed analyses (with a score of 14 as the cut-off point of remission), we intend to model the trajectory of scores across the 3.5-year observation period. This will permit the assessment of the severity of depression over time, with a particular focus on the 2-year follow-up period.

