### The analysis of data

To preserve neutrality, no data will be analysed until all subjects have reached the six month follow-up point. An intention-to-treat analysis will be performed in the first instance (i.e. analysing all available data from randomised participants) using for all analyses the STATA, version 11.0 package. The numbers and percentages of losses to follow-up at 12, 18, and 24 months after randomisation will be reported and will be compared between the treatment arms with absolute risk differences (95% CIs). Any deaths and their causes will be separately reported. To increase the power and precision of the estimated treatment effect, missing baseline covariates will be imputed for our main analysis using either mean or regression imputation [77]. All available results will be used without missing outcomes being imputed. Primary analyses will be based on the assumption of ignorable drop-outs. In secondary analyses, missing values will be replaced by multiple imputations using Markoff Chain Monte Carlo methods [78].

For continuous outcome variables, the differences in mean score between those randomised to either arm of the trial will be examined using analysis of covariance adjusting by 1) baseline value of outcome 2) baseline value of the outcome, gender and age. The assumption of linearity will be assessed by residual analysis; if necessary, bootstrapping techniques will be employed. Sensitivity analyses will be conducted to take into account missing data using multiple imputation, which assumes data are 'missing at random'. For continuous response variables, statistical analyses will be based on linear mixed models [79].

For binary responses, mixed-model logistic regression models and generalized estimating equations will be used [80]. Logistic regression will be used to compare proportions of patients that have lost their diagnosis during the treatment and follow-up period in the two groups using an HRSD of 14 as criterion. Analysis of 'time to first recovery' and ‘time to first relapse’ outcome will also be conducted using survival analysis methods and the log-rank test for bivariate comparisons and Cox's proportional hazards to adjust for gender, stratification variables and time spent on treatment prior to randomisation. The dependencies between design points in the case of linear mixed models will be accounted for by assuming an unstructured correlation structure.

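### The entry rule and the remission rule overlap at HRSD 14 and below, so the plan allows a participant to meet the remission criterion at randomisation

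*Protocol article*

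**What the plan says.** **Entry.** The abstract (Methods/Design) asks for "≥14 on the HRSD or ≥21 on the BDI-II". Under Recruitment & the determination of eligibility, the text after Table 1 says that two research interviews confirm that referrals "meet DSM-IV criteria for Major Depressive Disorder" and "show a minimum symptom severity score of 14 on the HRSD or 21 on the BDI-II". Either scale is enough.

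**Remission.** The abstract gives "RCT MAIN OUTCOME: HRSD (with ≤14 as remission". The Primary outcome section plans categorical depressed/not depressed analyses "with a score of 14 as the cut-off point of remission". The analysis of data section compares by logistic regression the proportions who no longer have their diagnosis "in the two groups using an HRSD of 14 as criterion". Only the abstract says on which side of the cut-off a score of exactly 14 falls.

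**Time to event.** The same section plans analyses of time to first recovery and time to first relapse; the text reads "outcome will also be conducted using survival analysis methods and the log-rank test". It defines neither event and states no condition for being at risk.

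**Baseline severity.** Minimisation (Randomisation section) uses BDI-II bands of 21–39 and 40 or more, not HRSD. Continuous outcomes are analysed by ANCOVA adjusted for the baseline value and by mixed models. Complementary analyses adjusting for baseline outcome levels are also planned.

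**The concern.** A remission endpoint should be one that nobody has reached at time zero. Here the rules allow it to be reached at entry in two ways:

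1. An HRSD of exactly 14 satisfies both the entry minimum and the abstract's remission rule.
2. Entry on BDI-II of 21 or more sets no HRSD floor, so any HRSD below 14 is possible. The minimisation bands start at BDI-II 21. If everyone randomised fits a band, everyone qualifies on BDI-II and the HRSD minimum excludes nobody.

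The requirement for SCID-I major depression sets no HRSD floor either. It makes the conflict sharper: at baseline the same person has a confirmed diagnosis and, by the analysis rule, has lost it.

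At stake is what the categorical comparison means. Participants already below the cut-off who stay there are counted as successes in both arms. This raises both remission rates and pulls the difference between arms towards zero. The abstract attaches the cut-off to the main outcome, and the categorical analysis sits under the Primary outcome heading, so it is not a minor endpoint.

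**Working it through.** **The overlap (logic only)**

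| Baseline HRSD | BDI-II | Eligible on severity? | Meets remission rule at entry? |
|---|---|---|---|
| 15 or more | any | yes, by HRSD | no |
| exactly 14 | any | yes, by HRSD | yes, under the abstract's ≤14 |
| below 14 | 21 or more | yes, by BDI-II | yes |
| below 14 | below 21 | no | – |

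The second and third rows show the fault. No assumption is needed for this step.

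**Inputs for the size**
- From Sample size, power calculation & primary outcome: a 35% difference, alpha 0.05, beta given as 0.9 (read as power 0.90), 80 cases in two equal arms before clustering.
- From The limitations of the trial: N = 129, so about 64 per arm.
- Assumed: that 35% means absolute points; a control remission rate of 20%, hence 20% v 55%; a two-sided test; and q, the share at or below 14 at entry who stay there in both arms.

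**The plan's own figure.** A pooled two-proportion calculation (two-sided 0.05, power 0.90, no continuity correction) for a 35-point difference gives a total of 78 at a control rate of 20%, 80 at 25% and 82 at 30%. The stated 80 is therefore reachable on this reading. The control rate is not stated, so it cannot be reproduced from the article's inputs alone.

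**Dilution**
- TAU: p₀ = 0.20(1 − q) + q
- PPD: p₁ = 0.55(1 − q) + q
- Difference: p₁ − p₀ = 0.35(1 − q)
- Power = Φ{[(p₁ − p₀)√n − 1.96√(2p̄(1 − p̄))] / √(p₀(1 − p₀) + p₁(1 − p₁))}, with n per arm and p̄ the mean of p₀ and p₁.

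For q = 10% and n = 40: p₀ = 0.28, p₁ = 0.595, p̄ = 0.4375. The numerator is 0.315 × 6.325 − 1.96 × 0.7016 = 0.617 and the denominator is 0.665. The ratio is 0.928 and the power 0.823.

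| q | TAU v PPD | Difference (points) | Power, 40 per arm | Power, 64 per arm |
|---|---|---|---|---|
| 0 | 20% v 55% | 35 | 0.91 | 0.99 |
| 5% | 24% v 57.3% | 33.3 | 0.87 | 0.98 |
| 10% | 28% v 59.5% | 31.5 | 0.82 | 0.96 |
| 20% | 36% v 64% | 28 | 0.72 | 0.90 |
| 30% | 44% v 68.5% | 24.5 | 0.60 | 0.80 |

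Both power columns ignore dropout and clustering. If only 80% of the overlapping group are at or below 14 at follow-up, equally in both arms, the difference is the same and power hardly moves (0.83 at q = 10% and 0.72 at q = 20%, with 40 per arm).

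**Plausible q.** The article gives no baseline HRSD distribution. Under an assumed normal distribution with mean 18 to 22 and SD 4 to 6, the share at or below 14 is Φ((14.5 − mean)/SD). This runs from 3% (mean 22, SD 4) to 28% (mean 18, SD 6). It is an illustration, not an estimate for this trial.

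**Restricting to baseline HRSD above the cut-off.** The difference returns to 20% v 55% with n(1 − q) per arm. With 40 per arm, power is 0.88 at q = 10% (n = 36) and 0.84 at q = 20% (n = 32). With 64 per arm it is 0.98 (n = 57.6) and 0.97 (n = 51.2). Under this model the smaller set has more power than the diluted full set.

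**The case against.** - **No affected participant is shown.** A reader might infer that some participants had in fact already remitted at entry. The article does not support that: it reports no baseline HRSD scores, and confirmed major depression with a two-year history makes low scores less likely. What stands is that the rules allow it.
- **Forty per arm is not the trial's size.** The article itself notes that 80 ignores therapist correlation, and its N is 129. At about 64 per arm the loss is modest. This is right, and is why both columns are shown. The article also calls the trial somewhat under-powered and expects high attrition, so the 64-per-arm column is optimistic.
- **The dilution model is near the worst case.** People with current major depression may worsen, and differently by arm, so they can carry treatment effect. This is fair: the factor 1 − q holds only if the overlapping group shows no arm difference.
- **Recovery and relapse are undefined.** One might conclude that recovery time is zero for these participants and that their relapse clock starts at randomisation. The text does not say so, and event definitions may sit in an analysis plan not shown. The point reaches the survival analyses only if recovery uses the same cut-off.
- **Baseline adjustment is planned.** It is, in complementary analyses, and the Cox model includes the stratification variables. But the severity stratifier is BDI-II, and adjustment does not put a person at risk of an event whose criterion is already met.
- **Restriction departs from intention to treat.** It removes randomised participants from one analysis, but by a value fixed before randomisation, so the arms remain comparable. An all-randomised sensitivity analysis answers the rest.

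**Conclusion.** The point stands as a fault in the stated rules. Entry on HRSD 14 or more, or BDI-II 21 or more, together with remission at HRSD 14 or below, lets an unchanged participant be counted as remitted, and nothing in the article removes that. The exact-14 case rests on the abstract's inequality. The BDI-II route does not: it leaves scores below 14 open however the boundary is read.

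The size is conditional. The remission difference shrinks by 1 − q if the overlapping group shows no arm difference, and q is unknown. The power figures also depend on the assumed 20% v 55%, on reading 35% as absolute points, and on the number per arm.

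The scope is the remission and loss-of-diagnosis comparisons, and time to first recovery if it uses the same cut-off. A reader might infer that the whole primary HRSD comparison is compromised. It is not: the ANCOVA, mixed-model and trajectory analyses of HRSD scores do not use the cut-off.

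**What to change.** 1. Reconcile the abstract, the eligibility text, the Primary outcome section and The analysis of data, and state on which side of the cut-off a score of exactly 14 falls. Moving the cut-off cannot close the gap alone, because the BDI-II route sets no HRSD floor.
2. Pre-specify that the remission, loss-of-diagnosis and time-to-first-recovery comparisons use randomised participants whose baseline HRSD is above the cut-off, and count time to relapse only after a recovery reached after randomisation.
3. Report the categorical result in all randomised participants, adjusted for baseline HRSD, as a sensitivity analysis.
4. Keep every participant in the continuous HRSD analysis, and report by arm how many were at or below the cut-off at baseline.

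The article bars any analysis until all participants reach the six-month follow-up, so this can be settled before results are seen. The cost is analysis wording, a somewhat smaller set for the categorical comparison, and slightly less favourable remission rates in both arms.

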### Randomisation

The secure, automated telephone randomisation was provided by the Clinical Trials Unit at University College London. Minimisation is necessary to limit the impact of factors that might moderate treatment response. A gender bias has been identified in unipolar depression: UK prevalence is estimated at 28 per 1000 in women compared to 24 per 1000 in men [47]; pre-treatment severity has been shown to affect treatment outcome [48]; and antidepressant medications are the most frequent treatment for depression. Therefore, a computer-generated, adaptive minimisation algorithm incorporating a random element was employed to control for gender, depression severity (BDI-II of 21–39 or of 40+) and medication (on/off). Only the information needed for the minimisation algorithm was provided to the Clinical Trials Unit.

### The test intervention

As described, the PPD intervention is 60 fifty-minute sessions of once-weekly individual psychoanalytic psychotherapy. Each treatment therefore lasts for 18 months. The therapists are all senior clinicians of the Adult Department of the Tavistock Clinic. They have a qualification in one of the core mental health disciplines of psychology, social work, nursing or psychiatry, plus a British Psychoanalytic Council approved training in psychoanalytic psychotherapy or psychoanalysis. All therapy sessions, as well as the therapist peer-supervision sessions, are audio-recorded.

#### *The PPD treatment manual*

[name] [49] has written a PPD treatment manual which describes the general principles of psychoanalytic psychotherapy, and the way in which they are applied to this patient group. The manual, which states the principles that should guide intervention, is permissive rather than prescriptive in its approach. Thus it authorises trained therapists to follow the direction of the patient’s narrative. In this the manual is representative of both psychoanalytic principles and current psychodynamic clinical practice [50]. The approach to manualisation of other evidence-based, longer term psychodynamic therapies employs a similar strategy [51].

As well as describing the aims and values of psychoanalytic treatment, the manual specifies the therapist’s tasks and purposes in relation to the TRD patient group. It outlines the kind of problems and conflicts found in this patient group; it emphasises the significance of the treatment framework, and it provides examples of session narratives (clinical material) typically encountered in depressed patients. The manual goes on to offer a number of psychoanalytic formulations of the expected components of depression, including the configurations underpinning chronicity and refractoriness. It illustrates the therapeutic approaches recommended in the opening, middle and ending phases of treatment. A specific section is devoted to management issues likely to arise with this patient group, including suicidal crises. The manual’s final section identifies those features which distinguish the PPD approach from other psychological interventions for MDD such as CBT. The manual has been adopted in a German multi-centre depression study [52].

#### *The assessment of treatment fidelity*

The PPD treatment is supported by fortnightly peer supervision and therapist workshops which are audio-recorded. The evaluation of treatment fidelity will use the Psychotherapy Process Q-Sort (PQS, [53,54]) a 100 item instrument distinguishing key actions, behaviours and therapists’ statements in different types of psychological therapy. Q-sort ratings are made according to a pre-determined normal distribution. This approach to the assessment of adherence has the advantage of being independent of the theoretical model of the treatment under evaluation. The degree of match of a given session to a psychoanalytic prototype can be quantified [55], and the absence of elements inimical to the test intervention confirmed. The instrument is valid. It has been widely used in similar investigations [56,57]. Trained raters independently score randomly selected samples of sessional material on a 1 to 9 scale in terms of resemblance to different psychological therapy prototypes. High levels of inter-rater reliability have been achieved [57-59] We expect the PPD treatment to score highly on the fostering of unstructured open-ended dialogue, use of transference interpretations, and the identification of unconscious processes. Low scores are expected for features of the CBT prototype such as the negotiation of foci on specified categories of thought and belief systems, encouragement of homework on particular issues outside the therapy and behavioural ‘experiments’.

### The treatment as usual condition

Patients randomly assigned to the TAU control group continue to receive treatment as directed by the referring practitioner. This may include referral for other specialist provisions. In the UK’s NHS, the range of such treatments is defined, and to an extent specified, in the treatment guidelines of the National Institute for Clinical Excellence [60]. Referral to psychoanalytic therapy is not within the guidance. Treatments and interventions received by the TAU control participants are recorded over the duration of the trial by using the Client Service Receipt Inventory (CSRI, [61]) and GP records. Arguments for and against this kind of comparison group are considered in the Discussion. At the end of their period of participation in the trial, the cases of all TAU participants are reviewed by the Tavistock’s Adult Department, with a commitment to offer PPD should it be indicated or requested.

### The outcome measures

#### *Primary outcome*

In psychotherapy and antidepressant medication outcome research, the Hamilton Rating Scale of Depression (HRSD, [44]) is the most widely used interview-based measure of depressive severity [62]. Independent, double-rated HRSD scores have been chosen as the trial’s primary index of depression severity. The HRSD is a structured interview which quantifies the severity of depressive symptoms in patients already diagnosed as suffering from depressive disorder. The psychometric properties of the instrument are acceptable [63]. In addition to categorical depressed/not depressed analyses (with a score of 14 as the cut-off point of remission), we intend to model the trajectory of scores across the 3.5-year observation period. This will permit the assessment of the severity of depression over time, with a particular focus on the 2-year follow-up period.

### Subsidiary outcomes

(a) **Self-report depression severity**: is assessed using the Beck Depression Inventory (BDI–II [64]) which is the most commonly used self-report instrument. It consists of 21 items, which yield a range of scores from 0 – 63. It has been shown to have excellent reliability (coefficient alpha of .92 for an outpatient population) and diagnostic efficiency [62,64].

(b) **Axis I disorders**: are assessed using the Structured Clinical Interview for DSM–IV, research version (SCID-I [65]). This semi-structured clinical interview assesses subjects on all five axes of DSM–IV diagnosis. The SCID-I, often considered the standard for clinical diagnoses [66], has acceptable inter-rater reliability (0.60 – 0.83; [67]). The diagnoses assessed in the TADS trial are MDD, dysthymia, alcohol abuse/dependency, drug abuse/dependency, anxiety disorders, OCD, and eating disorders.

(c) **Axis II personality disorders (PD)**: the Structured Clinical Interview for DSM–IV Personality Disorders Questionnaire (SCID-II-PQ [68]) is used to identify patients with probable Axis II disorders. This self-report measure has been found to have a 67% concordance with the SCID-II and strong associations have been reported between scores on the SCID-II and SCID-II-PQ for PD diagnostic concepts and categories (0.74 – 0.97 [only three under 0.80] [69]).

(d) **Personality functioning**: the information yielded by the Tavistock Psychodynamic Interview (TPI) allows Axis-II pathology to be assessed with the Shedler-Westen Q-Sort [42]. The information also permits the assessment of personality pathology according to the revised criteria of the proposed DSM-5. The TPI is described in more detail in the section below devoted to the qualitative part of the study.

(e) **Object relations**: the Person’s Relating to Others Questionnaire (PROQ2a [70]) is a 96-item self-report questionnaire which evaluates style of personal relating in terms of close (involving) vs. distant (seeking separation) and upper (relating from above downwards) vs. lower (relating from below upwards). The measure uses eight scales which are structured around these two axes. Birtchnell and Evans [71] have demonstrated that all scales have high internal validity (0.73 and above).

(f) **Social functioning**: the Global Assessment of Functioning scale (GAF, [72]) is a widely-used rating instrument which evaluates psychological, social and occupational functioning positioned on a hypothetical, 0 – 100 continuum of mental health - illness. It also comprises Axis V of the DSM-IV. GAF scores are made on the basis of the aggregated total of information available on the subject. A treatment trial similar to this one reported high inter-rater reliability (0.92) [72].

(g) **Subjective well-being**: is assessed using the Clinical Outcomes in Routine Evaluation – Outcome Measure (CORE-OM [73]). This 34-item self-report instrument assesses subjective well-being, symptoms, function, and risk. All domains show good internal reliability (of 0.75 – 0.95), convergent validity, and sensitivity to change [74]. The instrument has been widely used in the assessment of treatments offered by UK NHS Psychotherapy Departments [41].

(h) **Quality of life**: the Quality of Life Enjoyment and Satisfaction Questionnaire (Q-LES-Q [75]) is a self-report instrument consisting of 93 items grouped into eight quality of life areas - physical health, subjective feelings, work, household duties, school, leisure activities, social relationships, and general activities. Each item is rated on a 5-point scale of enjoyment/satisfaction over the previous week. Mean scores can be derived from the eight summary scales with a range from 0–100, with higher scores indicating better quality of life. The instrument achieves acceptable test–retest reliability (0.60 – 0.89). Its subscales show good levels of internal consistency (0.82 – 0.93 [76]).

(i) **Number of depression-free days**: at intake, and at all subsequent review/ follow-up interviews, participants are asked to estimate the number of depression-free days experienced in the preceding month

Table 2 lists all measures and the timing of their administration.

**Table 2 T2:** Frequency of the TADS primary and secondary outcome measures

Time point	BDI	HRSD	CORE	PROQ2	QlesQ	SCID-I	SCID-II-PQ	CSRI
**Baseline**	✔	✔	✔	✔	✔	✔	✔	✔
